A patient who is randomly allocated to the craniotomy group, but finally receives a decompressive craniectomy as a lifesaving action during the initial surgery, will be rejected from this randomized controlled trial. This potential selection bias is beyond the control of the investigators, and according to the current guidelines, no specific surgical options are provided for the enrolled participants. Nevertheless, patients’ detailed data will be recorded, providing the observational cohort information necessary to further analyze the possible factors and potential bias.

Due to the nature of the intervention, and the risk that DC surgical procedure will result in skull defect, patients and treating doctors cannot be blinded to allocation. However, the evaluators involved in this study and the investigators responsible for the outcomes’ analysis are blinded to the groups.

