### Data collection

Once patients are enrolled in the study, data related to demographic and clinical information, including hospital admission, treatment process, and follow-up, will be collected by the local investigators and recorded on the case report form (CRF). Detailed data consisting of neurological condition, timing of injury (also the ER, initial CT, and surgical operation), radiographic abnormalities, operation data, and postoperative care management (including ICP management and pharmacological data) will also be recorded. Postoperative CT scan will be performed routinely on the 1st, 3rd, and 7th day post-initial surgery. Cerebral infarction will be initially detected by postoperative CT image depicting a low-dense area. The blood supply of involved lobes will be further detected by transcranial Doppler sonography (TCD) and/or MR. Follow-up visits in the outpatient department are scheduled at 1, 3, and 6 months after injury; data will be collected and recorded. The information recorded on CRFs will be entered into an electronic data collection (EDC) database by a designated person within each participating center. A subject must be withdrawn from the trial if one of the following applies:
Each patient or his/her legally authorized representative has the right to require withdrawal from the study cohort for any reasons after enrollment.The investigator will withdraw a patient who is randomly allocated to a craniotomy and that eventually requires a DC as lifesaving action during the initial surgery.In addition, the investigator could withdraw the patients from their allocated treatment group if a clinical reason for not performing the surgical intervention is identified after randomization.Lost to follow-up.

The primary reason for all discontinuations and withdrawals will be documented.

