So far, there is no reliable data able to clarify the potential selection bias caused by the number of patients who, after initial allocation to a craniotomy, eventually require a DC. This study aims to be a pragmatic trial to improve and specify the surgical options for AEDH. Data of patients who, after initially undergoing craniotomy, eventually require a DC will be recorded, as the incidence of additional craniocerebral surgery after the initial surgical treatment (secondary endpoint). All these information will help in evaluating the potential selection bias.

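### Craniotomy patients converted to DC at the first operation are removed after randomisation, with no matching rule in the DC arm; this is likely to bias the primary GOSE comparison against DC

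*Protocol article*

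**What the plan says.** The section on sample size, randomization and blinding has eligible patients randomised through a central web system before surgery, with treating doctors unblinded. It then says that a craniotomy-allocated patient who "finally receives a decompressive craniectomy as a lifesaving action during the initial surgery, will be rejected from this randomized controlled trial". It concedes a problem but adds: "This potential selection bias is beyond the control of the investigators". For the removed patients, "patients’ detailed data will be recorded, providing the observational cohort information necessary to further analyze the possible factors and potential bias".

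The Data collection section repeats the rule in its list of circumstances in which a subject must be withdrawn: the investigator "will withdraw a patient who is randomly allocated to a craniotomy and that eventually requires a DC as lifesaving action" during the initial surgery. A further item in that list says that "the investigator could withdraw the patients from their allocated treatment group if a clinical reason for not performing the surgical intervention is identified" after randomisation. No item names DC-allocated patients whose bone flap is put back.

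The Data analysis section says that no reliable data exist on how many patients this will affect, and points to a secondary endpoint: "Data of patients who, after initially undergoing craniotomy, eventually require a DC will be recorded, as the incidence of additional craniocerebral surgery". The article calls the trial pragmatic, and it names no analysis population.

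**The concern.** A randomised comparison is protected only while membership of the analysed arms does not depend on what happens after allocation. Here it does, and in one arm only. A craniotomy-allocated patient who needs a lifesaving DC in theatre leaves the trial. A patient in the same state allocated to DC receives the allocated operation and is analysed. If converted patients tend to do worse, which the word lifesaving makes likely, the remaining craniotomy arm looks better than the strategy of allocating craniotomy really is. A true benefit of DC could then be understated, or an apparent harm could arise from nothing. For a pragmatic trial that asks which operation to plan, conversion is part of the craniotomy strategy's result.

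**Working it through.** **Reading the passages together.** The removal rule appears twice, once as a mandatory withdrawal. The secondary endpoint offered as a check is defined under Aims and outcomes as additional surgery for deterioration after the initial surgical treatment. A conversion during that first operation is not additional surgery after it, so the endpoint misses the patients in question. The same failure of craniotomy is removed if it shows in theatre, and is kept and counted if it shows later.

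**Inputs from the protocol.** Favourable outcome 93% (DC) and 72% (craniotomy); two-sided 5% significance; 80% power; 10% loss; 1:1 allocation; N = 120, so 60 per arm and 60 × 0.90 = 54 evaluable.

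**Planned sample size first.** With pooled variance, n per arm = [1.96√(2 × 0.825 × 0.175) + 0.842√(0.72 × 0.28 + 0.93 × 0.07)]² / 0.21² = 50.2, rounded up to 51. That is 102 in total, and 102/0.90 = 113.3, or 114. The calculated figure is not printed, but 114 enlarged to 120 fits the text. No sample-size error is asserted.

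**Assumed, because the documents do not say.** Let c be the share of the craniotomy arm converted, f the favourable rate in those patients, and p the craniotomy arm's rate as randomised. After removal:

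- analysed craniotomy rate = (p − c·f)/(1 − c)
- shift = c(p − f)/(1 − c), which is zero when f = p

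Rejection rates come from exact binomial enumeration of the pooled chi-square test, with 54 DC patients against 54(1 − c) craniotomy patients, rounded. The binary favourable outcome, on which N was based, stands in for the covariate-adjusted ordinal analysis.

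**No true difference.** Both arms are set at 82.5%, the midpoint of 93% and 72%.

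| c | f | Analysed craniotomy rate | Spurious difference against DC | Type I error |
|---|---|---|---|---|
| 5% | 60% | 83.7% | 1.2 points | 5.4% |
| 5% | 30% | 85.3% | 2.8 points | 6.7% |
| 15% | 50% | 88.2% | 5.7 points | 13.1% |
| 20% | 30% | 95.6% | 13.1 points | 53.5% |

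Third row worked: (0.825 − 0.15 × 0.50)/0.85 = 0.882. The last row is extreme: it needs 95.6% favourable in non-converted patients against 30% in converted ones.

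**Planned effect, two readings of 72%.**

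- *72% is the as-randomised craniotomy rate.* With c = 15% and f = 40%, the analysed rate is (0.72 − 0.06)/0.85 = 77.6%. The difference falls from 21 to 15.4 points and power from 85% to 62%. With c = 5% and f from 30% to 60%, power is 77% to 82%.
- *72% already excludes converted patients.* The analysed contrast stays at about 21 points. With c = 15%, power is about 83%, the loss coming from smaller numbers alone. The as-randomised craniotomy rate would then be lower, for example 0.85 × 72% + 0.15 × 40% = 67.2%. The contrast between strategies would be 93 − 67.2 = 25.8 points, which the analysed 21 understates.

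**The case against.** The strongest points on the other side are these.

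- *The size is unknown and may be small.* This stands. At 5% conversion the distortion is minor, and it vanishes if converted patients do as well as the rest. A reader might infer that the rule certainly strips out the worst cases, or that type I error will reach 53%. The documents support neither: converted patients' outcomes are not reported, and the second figure belongs to an extreme corner of the assumptions.
- *The loss of power may not occur.* This also stands. The 93% and 72% describe patients who received each operation in a retrospective study, so 72% may already exclude converted patients. The bias under no true difference remains on either reading.
- *The figures are for a binary test, not the ordinal primary analysis.* True. They illustrate direction and order of size only.
- *The other withdrawal item is limited.* A reader might take it as licence to withdraw anyone for any clinical reason. The text is narrower, requiring a reason "if a clinical reason for not performing the surgical intervention is identified after randomization", and it speaks of leaving the allocated treatment group, although the list's opening speaks of withdrawal from the trial. It is ambiguous rather than open-ended.
- *A separate analysis plan may define an intention-to-treat set.* It may, but it would then contradict two explicit statements here, and these would still have to change.
- *The data are recorded anyway.* Recording them as observational cohort information does not return these patients to the randomised comparison.

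**Conclusion.** The rule is wrong as written. It is explicit, stated twice, applies to one arm and acts after randomisation. Conversion may be unavoidable, but removing the converted patient from the comparison is a design choice, so the bias is not beyond the investigators' control. The likely direction is against DC, provided that converted patients fare worse than other craniotomy patients. On the assumptions shown, the spurious difference runs from about 1 point at 5% conversion to 5.7 points at 15% conversion with 50% favourable, and reaches 13 points only in an extreme case. The protocol itself says that no reliable data exist to narrow this range. The point concerns who is followed up and analysed, not whether or when a surgeon should convert.

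**What to change.** Replace the rejection sentence in the randomization section and the matching withdrawal item under Data collection with a rule that separates departure from the allocated operation from exclusion from the analysis:

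- The primary GOSE analysis includes all randomised patients in their allocated arm, subject only to the consent-withdrawal and data-deletion terms under Ethics and dissemination.
- 6-month GOSE is collected whatever operation was done.
- The same analysis rule covers patients who leave their allocated treatment for a clinical reason. The clinical ground itself is left unchanged.
- Intraoperative departures from allocation are reported by arm, as an item distinct from later additional surgery.
- Any per-protocol analysis is a sensitivity analysis only.

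The cost is more than wording. The amendment needs prior ethics approval. Recruitment began in September 2020, so converted patients already withdrawn may need their follow-up restored; the article promises detailed data on them but does not specifically promise 6-month GOSE. Crossover will dilute the contrast between the two operations somewhat, which is the price of a valid comparison of the two strategies.

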### Sample size calculation, randomization, and blinding

Our data and results from a previous retrospective study are showing that almost all the patients who received a synchronous DC (93%) had a GOSE of 6.63 ± 1.27, with a favorable outcome (defined by the GOSE categories: lower moderate disability, upper moderate disability, lower good recovery, and upper good recovery). Patients who received craniotomy had a GOSE of 5.78 ± 1.58, with a favorable outcome in 72% of the patients [6]. We calculated the sample required in this clinical trial with a significance level of 5% (two-sided) and a power of 80% to demonstrate the difference in the rate of favorable outcome, with an assumption that 10% of the patients would be lost during follow-up. Ultimately, considering the quality of the study, the sample size is enlarged to 120.

All participating centers must have a neurosurgical on-call team and an emergency department responsible for the admission of head-injured patients to identify eligible patients. After recording the patient’s clinical information, including Glasgow Coma Scale (GCS), pupillary reactivity, and CT findings, an electronic data collection (EDC) database will generate the subject identification number that will be allocated to the eligible patients. A secure central web-based randomization management information system will be used for the randomization of eligible patients. The system will provide an immediate allocation along with the patient randomization record number for the trial, and individual randomization record numbers can be checked at any time. Blocked randomization will be used, with a block size of 4 and an allocation ratio of 1:1. The 24-h central web-based randomization management information system will be backed by one delegated person (available 24 h per day) who will assure the cover-up of the record allocation. The delegated person responsible for randomization will not be involved in the treatment procedure. A confirmatory email will be sent to the investigator of each center involved to verify the allocation.

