### Aims and outcomes

The trial aims to evaluate craniotomy and DC on AEDH patients in terms of efficacy, economic benefits, and complications. The primary endpoint is the Glasgow Outcome Score-Extended (GOSE) at 6 months post-injury, the most commonly used prognostic evaluation scale in TBI, which allows the assessment of the long-term functional outcomes, including overall mortality and morbidity rates [8, 9].

Additionally, the following secondary endpoints are intended to be investigated as supplementary functional and cognitive measures:
The incidence of postoperative cerebral infarction within 6 months post-injury, to be primarily diagnosed by independent radiologists by CT or MRI examinationThe incidence of additional craniocerebral surgery, as a result of clinical deterioration after initial surgical treatment for AEDH, within 6 months post-injuryThe incidence of serious adverse events (SAE) within 6 months post-injury, and SAE is defined as an untoward occurrence that:
Results in deathIs life-threateningRequires hospitalization or prolongation of existing hospitalizationResults in persistent or significant disability or incapacityIs otherwise considered medically significant by the investigatorThe length of patient’s stay in ICU and hospital after initial surgery within 6 months post-injuryDetailed economic evaluation, defined as the total medical expenses related to the treatment for AEDH, including the costs of operations, hospitalization, and rehabilitation within 6 months post-injuryQuality of life at 6 months post-injury with the score of 5-level EuroQol Five Dimensions Questionnaire (EQ-5D-5L). The EQ-5D is a generic instrument to describe and evaluate the health condition on the basis of five dimensions: mobility, self-care, usual activities, pain/discomfort, and anxiety/depressionMMSE (Mini-Mental State Examination) scores at 6 months post-injury

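### Evaluator blinding is asserted, but the follow-up and imaging procedures described make it not credible for the GOSE and unattainable for infarction read on early postoperative CT

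*Protocol article*

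**What the plan says.** All references are to the protocol article.

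- **Sample size calculation, randomization, and blinding.** Because of "the risk that DC surgical procedure will result in skull defect, patients and treating doctors cannot be blinded to allocation". The next sentence says that "the evaluators involved in this study and the investigators responsible for the outcomes’ analysis are blinded to the groups". It does not say who the evaluators are or how the arm is hidden from them. The same section states: "A confirmatory email will be sent to the investigator of each center involved to verify the allocation".
- **Data collection.** Data, "including hospital admission, treatment process, and follow-up, will be collected by the local investigators". "Follow-up visits in the outpatient department are scheduled at 1, 3, and 6 months after injury". For imaging, "Postoperative CT scan will be performed routinely on the 1st, 3rd, and 7th day post-initial surgery", and infarction is first sought on these postoperative images as an area of low density.
- **Study design, Table 1.** The GOSE is marked at 1, 3 and 6 months, the same time points as the physical and neurological examination and imaging.
- **Treatment interventions.** Removal or replacement of the bone flap is the sole difference between the arms. Cranioplasty is normally recommended after DC; its timing is not given.
- **Aims and outcomes.** The GOSE at 6 months is the primary endpoint. Postoperative infarction, the first secondary endpoint listed, is "to be primarily diagnosed by independent radiologists by CT or MRI".

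**The concern.** The article treats a skull defect as enough to unblind patients and treating doctors, then states that the evaluators are blinded. The follow-up it describes would expose an evaluator to the same cue. A reader will take the statement as protection against detection bias, and the procedures do not supply that protection.

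The GOSE depends on judgement, and neighbouring categories can be hard to separate. The Data analysis section uses ordinal logistic regression across the full scale, so one-category shifts anywhere on it feed into the primary effect estimate. Expectation also has a direction: the retrospective data used for planning favor DC (GOSE 6.63 against 5.78; 93% against 72% favorable). A rater who knows the arm and those data could lean towards DC. The infarction endpoint is exposed in the same way, because the image that is read also shows the flap or its absence.

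**Working it through.** **1. The statements side by side.** The article states no figure for blinding, so this part is reasoning from the text.

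| Element | What the article says | Consequence |
|---|---|---|
| Who gathers follow-up data | Local investigators | Staff of the treating center |
| Who learns the allocation | The investigator of each center, by email | Known at the center |
| Setting | Outpatient department | A skull defect may be seen or felt |
| Timing of GOSE | Same time points as examination and imaging | Nothing described keeps scoring apart from these cues |
| Difference between arms | Bone flap out or in | The cue is the treatment itself |
| GOSE assessor | Not identified | Separate masked assessors are neither described nor excluded |
| State of the skull at 6 months | Cranioplasty recommended, timing not given | Defect present in an unknown share of DC patients |
| Infarction reader | Independent radiologist | Independence is not masking |
| Scans for infarction | CT on days 1, 3 and 7 | Presence or absence of the flap is on the image |

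For the GOSE, the described route gives several ways to learn the arm and no barrier. For infarction on the early CTs, no barrier is possible short of altering the images, and none is described.

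**2. Size, under stated assumptions only.** The documents give no rate of biased rating.

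*Mean GOSE.* The planning difference is 6.63 − 5.78 = 0.85. Assume that knowledge of the arm moves 15% of DC patients up one category. The mean then shifts by 0.15 × 1 = 0.15, and 0.15 / 0.85 = 18% of the planning difference. The shift is proportional to the assumed share.

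*Favorable rate.* The planned difference is 93 − 72 = 21 points. The line between unfavorable and favorable lies between GOSE 4 and 5. Assume that a quarter of the DC patients at GOSE 4 are rated across it.

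- The share at GOSE 4 is not stated. The maximum-entropy distribution on 1 to 8 that matches the DC mean of 6.63, SD of 1.27 and 93% favorable puts 5.3% there. A quarter is 5.3 / 4 = 1.3 points.
- Those three summaries do not fix the share. Distributions that match all of them allow anything from 0% to 7%, the ceiling being the whole unfavorable group (100 − 93 = 7). A quarter is 0 to 7 / 4 = 1.75 points.
- The shift is therefore about 1 point (0 to 1.75) of the planned 21.

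*False-positive rate of the binary secondary analysis.* Take 54 evaluable patients per arm (60 less 10%), no true difference, a two-sided 5% test with pooled variance, and an upward rating bias of *b* points in one arm:

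| *b* | Base rate 72% | Base rate 80% |
|---|---|---|
| 2 points | 5.6% | 5.8% |
| 5 points | 9.1% | 10% |
| 10 points | 23% | 31% |

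These rows show how sensitive the test is. They do not estimate what will happen in this trial.

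**The case against.** The strongest reply is that the article separates two groups: patients and treating doctors, who are not blinded, and evaluators and analysts, who are. That is not a contradiction in itself. The sentence about local investigators concerns gathering data onto the case report form and does not say that they score the GOSE. Table 1 shows when the GOSE is due, not who rates it or by what means. A journal article may leave rater identity, interview script and masking method to the full protocol.

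Much of this stands. A reader might infer that evaluator blinding cannot hold at all. The article does not support that, because separate assessors masked by a remote interview are compatible with its text. A reader might also infer that every scan and every visit reveals the arm. Cranioplasty is recommended after DC, so some later scans and visits may not. The radiologists are called independent, not blinded, so the blinding sentence may not have been meant to include them. The analysts' blinding is not touched by any of this.

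It is also tempting to add the shift from rating craniotomy patients at GOSE 4 upwards, which would be a larger number. That would favor craniotomy and narrow the gap, the opposite of the suspected lean, so it does not belong in the estimate.

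What the reply does not remove is that the article asserts a protective property while every procedure it describes points the other way. This goes beyond missing detail.

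**Conclusion.** The point holds in this form: evaluator blinding is stated without a mechanism and is not credible under the follow-up described, though it is not shown to be impossible for the GOSE. For infarction read on the day 1, 3 and 7 CTs, any reader can tell the arm, so a blinding claim cannot extend to that reading.

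The size of any bias is unknown. The 18% of the mean planning difference and the roughly 1 point (0 to 1.75) of the favorable-rate difference rest on an assumed 15% of DC patients and an assumed quarter of those at GOSE 4, respectively. The conclusion about credibility rests on neither figure. It should be put right because the primary outcome depends on judgement and the remedy is cheap.

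**What to change.** 1. Reconcile Table 1 and the sections on randomization and blinding, Aims and outcomes, and Data collection, so that they agree on who scores the GOSE, where, and with what knowledge of the arm.
2. Have the evaluators already planned, outside the treating team and without access to the allocation, obtain the 6-month GOSE by a scripted structured telephone interview or questionnaire that bars mention of the operation or the skull. Make that score the primary endpoint.
3. Record each rater's guess of the allocation and report it by arm.
4. Word the blinding claim so that it does not cover infarction reading on postoperative CT. Rely there on a fixed written imaging definition (territory, size, new compared with the preoperative scan). The claim for the outcome analysts can stay.

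The cost is protocol wording, a script, and one call or questionnaire per surviving patient among the 120. The downside is that the primary score loses information from the physical examination, which can still be recorded at the clinic visit. No treatment is affected.
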